#### 11.1.2 Secondary Objective

The secondary objective of this study is to determine the antibody response of the combination vaccine to the AMA1 and MSP142 proteins as measured by antibody levels and growth inhibition.

Anti-AMA1 and anti-MSP142 antibody will be measured by ELISA on Study Days 0, 14, 56, 70, 180, and 194, 270, and 360. Peak antibody responses and longevity of response will be shown graphically. Antibody responses between the dose groups (US) and vaccine groups (Mali) will be compared. The primary antibody response will be the change from Day 0 to Day 42 antibody response, and Wilcoxon rank sum tests will be performed. Similar tests for changes between Day 0 and other Study Days will be performed as exploratory analyses. Immunogenicity in US adults (greater than 4-fold increase in antibody titer from baseline to peak response) is expected to be demonstrated. In Mali, interpretation of immunogenicity data is more difficult given pre-existing antibody titers and the likelihood of natural malaria infection during the study, and whether or not a significant difference in antibody response is detected between the groups will not be a determining factor for further studies. In Mali, if a difference in antibody response between the groups is detected, it will be described. However, this study is powered for safety

data alone, and whether or not a significant difference in antibody response is detected between the groups in Mali will not be a determining factor for further studies in children.

Graphs will display parasite growth inhibition expressed as a percentage of inhibition. Non-parametric methods will be used to compare inhibition as a function of treatment group and clone and to examine correlations between levels of antibody as judged by ELISA with GIA activity.

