#### 1.1.7 AMA1-C1/Alhydrogel®

There have been 4 human clinical trials to date using the recombinant AMA1-C1/Alhydrogel® vaccine.

The first clinical trial to use AMA1-C1/Alhydrogel® was performed at Johns Hopkins University (Baltimore, MD) [11]. Thirty subjects received up to 3 immunizations (Study Days 0, 28, and 180) with 5, 20, or 80 µg doses of AMA1-C1/Alhydrogel® in an open-label dose escalating study. No safety concerns were identified. Adverse events related to vaccination were limited to local injection site reactions, which were mild to moderate in severity. There was a dose response with the 80 µg group giving the highest antibody levels at Study Day 42 (14 days after the second vaccination) and at Study Day 194 (14 days after the third vaccination).

The second clinical trial using AMA1-C1/Alhydrogel® was started in Mali in May 2004. This study was a randomized, double blind, controlled trial [35]. Fifty-four healthy Malian adults were randomized 2:1 to receive either AMA1-C1/Alhydrogel® at 5, 20, or 80 µg doses, or the

Recombivax® Hepatitis B vaccine. Study participants received 3 immunizations on Study Days 0, 28, and 360. No vaccine-related serious or Grade 3 events were observed. AMA1 antibody responses to the 80 µg dose increased rapidly from baseline levels 14 and 28 days after the first vaccination and continued to increase after the second vaccination. Anti-AMA antibody levels peaked 14 days after the second vaccination then declined, reaching baseline levels 1 year later at the time of the third vaccination. Unlike the second vaccination, the third vaccination induced little or no increase in antibody levels.

The third trial was conducted at the NIH Clinical Center (Bethesda, MD). This study planned to vaccinate 12 healthy adults with 80 µg of AMA1-C1/Alhydrogel® and 6 with Alhydrogel® alone. Enrollment was closed at 6 volunteers due to difficulty with recruitment; 4 volunteers received AMA1-C1/Alhydrogel® and 2 received Alhydrogel®. The objectives of this study were to observe B-cell responses to vaccination. No safety concerns were identified with the 6 volunteers vaccinated.

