## **CLINICAL MONITORING AND EVALUATION**

Note: Vaccinations will be given on a 0, 2, and 6 month schedule in the US, and a 0, 2, and 4 month schedule in Mali, to allow for the third vaccination to occur just prior to the malaria transmission season in Mali.

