**Study Day 28  $\pm$ 3 Days**

1. Perform directed history and assessment of any physical complaint.
2. Record vital signs.
3. Obtain urine for dipstick test.

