**Study Day 56  $\pm$ 7 (Day of Second Vaccination)**

1. Perform basic history and focused physical examination, emphasizing examination of any acute complaints.
2. Mali only: during the physical examination, study staff will educate the subject regarding signs and symptoms of potential AEs, and indications for use of antipyretics

- (acetaminophen/paracetamol, or ibuprofen) if fever, headache, or malaise occurs.
3. Obtain approximately 40 (35 in Mali)mL of blood for CBC with differential and platelet count, ALT, creatinine, anti-AMA1 and anti-MSP142 antibody ELISA, and B cell studies.
  4. Obtain blood for malaria smear and filter paper collection (Mali only).
  5. For females, obtain a urine or serum sample for  $\beta$ -hCG testing. Ensure that the test is negative before vaccinating; a positive test will exclude the subject from the trial.
  6. Obtain a urine sample for dipstick testing and ensure that protein and blood are no more than trace positive before vaccinating. Should a female subject be menstruating on Day 56, she will not be excluded from vaccination if she has more than trace blood in her urine.
  7. Obtain urine for chloroquine testing (Mali only).
  8. Record vital signs (blood pressure, temperature, heart rate, and respiratory rate).
  9. Administer the vaccine.
  10. Observe for at least 30 minutes after vaccination to evaluate for immediate adverse reactions.
  11. US only: Review of proper use of digital thermometer, injection-site reaction measurement tool, and memory enhancement tool (diary) by study staff during 30-minute post-immunization wait period. Study staff will also discuss signs and symptoms of potential AEs, and indications for use of antipyretics (acetaminophen/paracetamol, or ibuprofen) if fever, headache, or malaise occurs.

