**Study Day 70 $\pm$ 2 Days (14 Days after Second Vaccination)**

1. Perform basic history and focused physical examination (including injection site), emphasizing examination of any acute complaints.
2. Record vital signs.
3. Obtain urine for dipstick testing. Obtain urine or serum for  $\beta$ -hCG testing.
4. Obtain approximately 40 mL of blood for CBC with differential and platelet count, ALT, creatinine, anti-dsDNA, anti-AMA1 and anti-MSP142 antibody ELISA, T cell studies, and GIA.
5. Obtain blood for malaria smear and filter paper collection (Mali only).

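### The lead antibody comparison is set at Day 42, when no sample is taken at either site; Day 70 is the likely intended day and should be confirmed before results are seen

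*Protocol*

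**What the plan says.** Section 11.1.2 (Secondary Objective) states when antibody is measured: "antibody will be measured by ELISA on Study Days 0, 14, 56, 70, 180, and 194, 270, and 360". It then fixes the lead comparison: "The primary antibody response will be the change from Day 0 to Day 42 antibody response, and Wilcoxon rank sum tests will be performed". The comparison is between dose groups in the US and between vaccine groups in Mali. The next sentence sets the status of every other day: "Similar tests for changes between Day 0 and other Study Days will be performed as exploratory analyses".

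Section 6.5 (Clinical Monitoring and Evaluation) gives the dosing: "Vaccinations will be given on a 0, 2, and 6 month schedule in the US, and a 0, 2, and 4 month schedule in Mali". The Day 56 visit is headed "Day of Second Vaccination" and the Day 70 visit "14 Days after Second Vaccination". Both include an ELISA draw. The visit before Day 56 is Day 28, which consists of "Perform directed history and assessment of any physical complaint", vital signs and a urine dipstick, with no blood drawn. Appendix B shows the same pattern.

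**The concern.** The sentence that names the lead antibody response refers to a day missing from the sampling list in the same section, from the visit descriptions and from the schedule table. Taken literally, the one ELISA contrast not labelled exploratory has no data.

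What is at stake is which time point leads. The available substitutes measure different things. Day 56 is drawn on the day of the second dose and reflects one dose. Day 70 follows two doses. Day 194 in the US and Day 134 in Mali follow three. If the day is settled only after results are known, the reported lead comparison could be the most favourable of several. The US part is open label, so group membership would also be known.

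**Working it through.** **The plan's own figure.** The protocol attaches no power or sample size to the antibody comparison. Its only sample-size figure concerns safety (Section 11.2): 12 per group and an event probability of 0.125 give 1 − (1 − 0.125)^12 = 1 − 0.875^12 = 0.799, matching the stated 0.80. It does not depend on the antibody time point.

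**Does any ELISA window contain Day 42?** Each window is the nominal day ± the allowance in Section 6.5.

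| ELISA draw | US window | Mali window |
|---|---|---|
| Baseline | 0 | 0 |
| Day 14 ± 2 | 12–16 | 12–16 |
| Day 56 ± 7 (dose 2) | 49–63 | 49–63 |
| Day 70 ± 2 | 68–72 | 68–72 |
| Dose 3: US 180 ± 14, Mali 120 ± 14 | 166–194 | 106–134 |
| 14 days after dose 3: US 194 ± 2, Mali 134 ± 2 | 192–196 | 132–136 |
| Later: US 270 ± 14, Mali 210 ± 14 | 256–284 | 196–224 |
| Day 360 ± 14 | 346–374 | 346–374 |

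None contains Day 42.

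**Does any clinic visit contain it?** The last visit before is Day 28 ± 3, ending at Day 31, which is 42 − 31 = 11 days short. The next is Day 56 ± 7, opening at Day 49, which is 49 − 42 = 7 days late. A footnote to Appendix B gives a different range for the second dose, Day 56 to 65; that does not reach Day 42 either. Scheduled Day 42 samples: 0 of 60 participants.

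**What would a Day 42 sample measure?** It would fall 56 − 42 = 14 days before the nominal second dose, and 7 days before the earliest date Section 6.5 allows. It would be a one-dose response.

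**Where might Day 42 come from?** In the first AMA1-C1/Alhydrogel trial (Section 1.6.1 in the table of contents), dosed on Days 0, 28 and 180, the 80 µg group gave the "highest antibody levels at Study Day 42 (14 days after the second vaccination"). There, 28 + 14 = 42. In this trial the same interval gives 56 + 14 = 70. Two other items fit a second dose on Day 28: the Day 63 visit asks for review of diary days 28 to 34, and the Appendix B footnote on vaccination timing uses Day 29 for the day after the second dose.

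**How much could a late choice matter?** Each site has seven post-baseline ELISA days. As an illustration, assume a 0.05 level, which the protocol does not state. Choosing the best of seven independent tests gives a false-positive chance of 1 − 0.95^7 = 0.30. Repeated measurements on the same people are correlated, so the true figure lies between 0.05 and 0.30.

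**Related mismatch.** After Day 70 the ELISA list in Section 11.1.2 gives 180, 194, 270 and 360, which are the US days. The Mali visits draw ELISA on 120, 134, 210 and 360. The Mali visits on Days 180 and 270 take malaria smears and filter paper but no ELISA sample.

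**The case against.** The strongest reply concerns weight, not fact. Antibody response is a secondary endpoint and the primary endpoint is adverse events. Section 11.1 describes the study as exploratory, and Section 11.1.2 says it is powered for safety alone and that an antibody difference in Mali will not decide further studies. No halting rule, dose-escalation step or sample-size figure uses the Day 42 contrast. All of that stands.

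A reader might infer three stronger things that the documents do not support.

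- *That the antibody evaluation as a whole fails.* Section 11.1.2 also plans the same tests at other days, a more-than-4-fold rise from baseline to peak in US adults, and growth inhibition comparisons and correlations. None needs Day 42. US immunogenicity does feed the plan to move to children (Sections 1.6.8 and 12.3), but the only immunogenicity criterion stated is the rise to peak.
- *That the day must be chosen after the results.* The samples are collected whatever this sentence says. An amendment, or an analysis plan not shown here, could fix the day in time. Post hoc choice is a risk if nobody acts, not a certainty.
- *That Day 70 is certainly what was meant.* The protocol never says so. The carry-over from a 0/28-day schedule is a well-supported inference, but the trial also samples 14 days after the third dose.

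The contradiction itself survives. It lies within one section of the protocol, and broken tables or removed text do not explain it.

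**Conclusion.** The point holds in limited form. The comparison named as the primary antibody response, which is the lead comparison of the secondary objective, cannot be run as written at either site. Until the text is corrected, no ELISA time point has lead status, because every sampled day is labelled exploratory.

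The absence of a Day 42 sample follows directly from the protocol and needs no assumption. That Day 70 is the right replacement assumes that 14 days after the second dose was intended, which is for the sponsor to confirm. The safety primary endpoint, the rise to peak, the growth inhibition analyses and the sample size are unaffected.

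**What to change.** In Section 11.1.2, replace the Day 0 to Day 42 change with the change from Day 0 to Day 70 (14 days after the second vaccination) for both sites. The sponsor should confirm that this is the intended day, and the amendment should be dated before antibody results are examined. Keep changes to the other days as exploratory.

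In the same edit, give the ELISA days by site: Days 0, 14, 56 and 70 for both; then 180, 194, 270 and 360 in the US; and 120, 134, 210 and 360 in Mali.

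The cost is a small text amendment. ELISA and growth inhibition samples are already drawn on Day 70 at both sites, so no visit, blood volume or sample-size figure changes.

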## 11. STATISTICAL CONSIDERATIONS

### DESCRIPTION OF STATISTICAL METHODS

This study, like other Phase 1 studies, is basically exploratory rather than confirmatory; its purpose is to estimate AE rates and patterns of immune responses rather than to test formal statistical hypotheses. Estimates will be presented with their 95% confidence intervals.

Descriptive approaches will be used to meet the protocol objectives as stated in **Section 2** of this protocol, as well as formal statistical tests as outlined below. Results will be presented in tabular format, as well as graphically where appropriate.

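### The Mali antibody difference should be reported with its 95% confidence interval whatever the test shows; the protocol promises to describe it if a difference is detected

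*Protocol*

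**What the plan says.** Section 11.1 (Description of Statistical Methods) describes the trial as exploratory and says "its purpose is to estimate AE rates and patterns of immune responses rather than to test formal statistical hypotheses". It adds, without exception for site or endpoint: "Estimates will be presented with their 95% confidence intervals".

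Section 11.1.2 (Secondary Objective) makes three commitments without condition: "Antibody responses between the dose groups (US) and vaccine groups (Mali) will be compared"; for the change from baseline, "Wilcoxon rank sum tests will be performed"; and "Peak antibody responses and longevity of response will be shown graphically".

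For Mali it then says "In Mali, if a difference in antibody response between the groups is detected, it will be described". Just before, it explains that Malian data are harder to interpret because of pre-existing titres and natural infection, and that "whether or not a significant difference in antibody response is detected between the groups will not be a determining factor for further studies". Just after, it says "However, this study is powered for safety" data alone and repeats that the antibody result will not determine further studies.

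**The concern.** The sentence makes description of a treatment difference depend on the result of a test, in a trial whose stated aim is to estimate. The only method that Section 11.1.2 names for the antibody comparison is a rank sum test, which yields a p-value. No difference, ratio or other between-group measure is named.

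Someone who follows the sentence literally could report a non-significant Mali result as no difference, with neither size nor uncertainty. A significant result would be described from a sample that had to be extreme enough to pass the test.

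Sections 3.1 and 6.3 give better interpretation of antibody responses as a reason for having the comparator arm. Titres in the vaccine arm alone cannot separate vaccination from exposure, so the between-arm difference is the quantity that serves this reason.

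**Working it through.** **1. What *detected* means.** The same section twice uses the verb for a significant difference, once before and once after the conditional sentence. Significance is the natural reading, but the protocol does not define the term.

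**2. The protocol's own figure.** The only power-type figure is for safety, in Section 11.2: 12 per group, event probability 0.125, chance of at least one event 0.80. Check: 1 − 0.875^12 = 0.799, which agrees. With 15 per group it is 1 − 0.875^15 = 0.865. Nothing comparable is given for antibody.

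**3. Inputs for the antibody contrast.** Section 3.1 gives 30 participants randomised 1:1, so 15 per arm. Section 11.1.2 gives the Wilcoxon rank sum test. The SD, effect size, significance level and sidedness are not stated. A two-sided 5% test and normally distributed data are assumed below.

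**4. Why selection inflates the estimate.** The standard error of a difference in means is SD × √(2/15) = 0.365 SD. With the t quantile 2.048 on 28 degrees of freedom, an observed difference must exceed roughly 2.048 × 0.365 = 0.75 SD to be significant (the t-test threshold, as an approximation to the rank test). If the truth is 0.5 SD, a described estimate is therefore too large almost by construction.

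**5. Simulation in SD units** (15 per arm, 6000 runs per case):

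| Assumed true difference | Detected | Mean estimate when detected | Overstatement |
|---|---|---|---|
| 0.3 SD | 11% | 0.84 SD | 0.84/0.3 = 2.8 times |
| 0.5 SD | 24% | 0.94 SD | 0.94/0.5 = 1.9 times |
| 0.8 SD | 53% | 1.05 SD | 1.05/0.8 = 1.3 times |
| 1.0 SD | 71% | 1.17 SD | 1.2 times |

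At 1.5 SD detection is 97% and the overstatement about 1%. With 12 per arm, the number Section 11.2 sizes on, a 0.5 SD difference is detected 19% of the time and overstated 2.1 times.

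**6. The same question in fold ratios** (15 per arm, 4000 runs, assumed SD of log10 change):

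| True ratio | SD 0.3 | SD 0.5 | SD 0.8 |
|---|---|---|---|
| 2-fold: power | 71% | 34% | 15% |
| 2-fold: mean ratio when significant | 2.2 | 3.1 | 5.3 |
| 4-fold: power | above 99% | 86% | 47% |
| 4-fold: mean ratio when significant | 4.0 | 4.4 | 6.8 |

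Across assumed ratios of 1.5 to 4 and SDs of 0.3 to 0.8, power runs from about 9% to above 99%.

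**7. What unconditional reporting would show.** The 95% interval multiplies and divides the ratio by 10^(2.048 × SD × 0.365). That is a factor of about 1.7, 2.4 or 4.0 for SDs of 0.3, 0.5 and 0.8. Such intervals are wide but informative.

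**The case against.** The strongest reply is that the two sections can be followed together. A reader might infer that the Mali estimate is reported only when significant, or that Section 11.1.2 contradicts Section 11.1. The text supports neither. It does not say that the estimate or interval is withheld otherwise; the general interval rule is not revoked; and the comparison, tests and graphs are planned unconditionally. In context the sentence may be meant as a caution on interpretation. This stands, and it limits the point to poor wording that could be followed literally.

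A reader might also infer that the trial has low power for this contrast. That is not shown. The protocol claims power for safety alone, and without an SD, effect size or significance level, antibody power cannot be computed. The roughly 2.5-fold figure in the account of earlier human experience compares AMA1-C1/Alhydrogel with and without CPG 7909 in Mali, which is a different contrast.

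Nor is this the only randomised immunogenicity comparison: growth inhibition is also compared by treatment group, with no such condition.

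Finally, effect measures and interval methods are often left to a statistical analysis plan. That is fair as regards the missing measure, but the conditional sentence is in the protocol, and a plan written to match it could carry it forward.

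**Conclusion.** The point holds as a wording fault with a modest consequence. The protocol ties description of the Mali antibody difference to its detection, most naturally meaning statistical significance, and this fits poorly with its own estimation purpose and interval rule.

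The distortion arises only if the sentence is taken literally, and its size rests on assumed effects. It is material for small to moderate differences (about 1.9 times at 0.5 SD, 1.3 times at 0.8 SD) and negligible for large ones. The harm is to reporting and interpretation of a secondary endpoint; the protocol says that this result will not determine further studies.

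**What to change.** Replace the conditional sentence in Section 11.1.2 with:

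*In Mali the BSAM-2 versus Euvax B difference in change from Day 0 in log antibody level, expressed as a ratio (for example the Hodges-Lehmann estimate matching the Wilcoxon test), will be reported with its 95% confidence interval for each antigen at the primary antibody time point, whether or not it is statistically significant.*

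Two details need settling for this to define one estimate:

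- **Time point.** Section 11.1.2 takes the change to Day 42 as primary, but neither its own list of sampling days nor Appendix B has a Day 42 sample. The primary day must be reconciled with the visit schedule and be one on which serum is drawn in Mali. Section 6.5 gives antibody samples there on Days 0, 14, 56, 70, 120, 134, 210 and 360.
- **Scale.** The Wilcoxon test should be run on the change in log level, so that test and estimate match. Ranks of raw changes and of log changes can differ.

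Keep the statement that the result will not determine further studies. The cost is one sentence and one more analysis, with no added participants or samples. The reported result may look less striking.

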#### 11.1.3 Exploratory Objectives

- To determine the extent to which antibody response to the AMA1 and MSP142 antigens is correlated when the combination vaccine (BSAM-2/Alhydrogel®+CPG 7909) is given.
- To determine T- and B-cell responses to vaccination.

T- and B-cell responses at different study days will be shown graphically for each dose group (US) or treatment group (Mali).

Should the study be terminated early (see **Section 9.5**), the investigative team will discuss with the SMC the reason for termination and determine which study questions can be addressed in an unbiased manner with the available data. The available data will be analyzed and interpreted in light of early termination.

#### **SAMPLE SIZE AND POWER CALCULATIONS**

The study is powered to provide sufficient safety data before proceeding step-wise (first dose ranging in the US, and then to Malian adults) towards the target population (young children in an endemic area). A sample size of 12 in each group gives a probability of 0.80 for detecting 1 or more adverse events that occur with a probability of 0.125 per subject. We have included 15 per dose group in case of withdrawals or loss to follow-up.

